## Abstract

**Background:**

Social anxiety disorder (SAD), also known as social phobia, is one of the most common mental disorders worldwide. In Hong Kong, the prevalence of SAD is high, but its treatment rate is low. SAD has immense impact on academic or work performance, social life, career development, and quality of life. One of the most effective treatments for SAD is cognitive behavioral therapy (CBT), with internet-based CBT (iCBT) and virtual reality exposure therapy (VRET) showing promise in treating SAD. However, internet interventions are underdeveloped in Chinese communities including Hong Kong.

**Objective:**

This study aims to develop an iCBT program that includes VRET, called “Ease Anxiety in Social Event Online” (Ease Online), for Hong Kong adults with SAD in a randomized controlled trial.

**Methods:**

The 14-week Ease Online program is a guided self-help iCBT program with a blended mode of service delivery. The program comprises 9 web-based modules and 5 individual counseling sessions (including 2 VRET sessions) conducted remotely or face-to-face with a therapist to provide therapist support, as guided iCBT shows superior effects than unguided iCBT. Other program components include therapist feedback on assignments, internal messages, forums, client portfolios, web-based questionnaires, reminders, and web-based bookings. The program can be accessed either through a mobile app or program website through a PC with an internet connection. The participants are openly recruited and screened using a questionnaire and through an intake interview. Eligible participants are randomized by placing them into a web-based iCBT group, app-based iCBT group, or a waitlist control (WLC) group. Participants in the WLC group are assigned to the app-based program upon completion of the service of the 2 experimental groups. Measurements of social anxiety, depression and anxiety symptoms, psychological distress, automatic thoughts, and quality of life are administered at pretest, posttest, and 3- and 6-month follow-ups. Multivariate ANOVA with repeated measures will be performed to determine the intervention effectiveness on the continuous variables over time.

**Results:**

Participant recruitment commenced in January 2021. As of February 2023, a total of 1811 individuals applied for the Ease Online program. In total, 401 intake interviews have been completed, and 329 eligible participants have joined the program, among whom 166 have completed the service. Data collection is still ongoing, which is expected to be completed in March 2024.

**Conclusions:**

This study is the first of its kind in combining iCBT and VRET for the treatment of SAD in Hong Kong. At a theoretical level, this study contributes to the development and evaluation of internet-based psychological interventions in Hong Kong. At a practical level, the Ease Online program may serve as an alternative service option for SAD clients in Hong Kong if proven effective.

**Trial Registration:**

ClinicalTrials.gov NCT04995913; https://clinicaltrials.gov/study/NCT04995913

**International Registered Report Identifier (IRRID):**

DERR1-10.2196/48437

## Introduction

### Background

Social anxiety symptoms have increased significantly during the COVID-19 pandemic [1]. Social anxiety disorder (SAD) is one of the most common mental health problems, yet few seek treatment [2]. Individuals with SAD experience excessive fear and anxiety during social interactions, which is disproportionate to the social situation itself. SAD often involves negative evaluation and rejection by others and a constant fear of embarrassment or humiliation [3]. Therefore, individuals with SAD often avoid social interactions, which may have detrimental impacts on most areas of life, including their career, education, social relationships, and mental health [4]. Social anxiety usually emerges during performance situations (such as job interviews, public presentations, or attending a meeting) and interpersonal situations (such as greeting someone, drinking and eating in public, taking part in social gatherings, or shopping). In Hong Kong, the 12-month prevalence rate of SAD is reported to be 3.2% [5], which translates into an estimated 230,000 cases. However, only 8.7% of people with SAD in Hong Kong had previously sought treatment [5].

People with SAD face certain treatment barriers that prevent them from seeking mental health services, including fear of judgement, uncertainty of the resources for receiving help, and skepticism regarding anxiety disorders [6]. In Hong Kong, the barriers also include the social and self-stigmas of mental illnesses, long waiting lists for public health care, and exorbitant costs of private treatment. However, people with SAD consider the internet as a good social outlet, which not only helps them to alleviate their fear during general social interactions but also meets their social needs [7].

Cognitive behavioral therapy (CBT) is the first-line treatment for SAD [8]. Clark and Wells [9] proposed a cognitive model of social anxiety that considers social cognition, safety behaviors, self-focused attention, and somatic symptoms as the maintaining factors of social anxiety. Thus, the effective treatment components of CBT for SAD primarily include exposure to fearful conditions, cognitive restructuring, attentional bias modification, and relaxation and social skills training [10]. Telemental health services, including internet-based CBT (iCBT) and virtual reality exposure therapy (VRET), have become a worldwide trend for the treatment of mental health problems, particularly SAD, which can reduce the therapist’s time required for each client [11]. For example, the average time spent in VRET is 8 minutes per session [12], and the therapist’s time in iCBT can be saved by more than half for the same level of reduction in social anxiety [13].

### iCBT for SAD

iCBT is used to deliver CBT on the web or through a mobile app. In a recent meta-analysis study, Andrews et al [14] showed that there are no significant differences between iCBT and face-to-face CBT in their efficacy for treating anxiety and depressive disorders, thus indicating equivalent overall effects elicited by both types of treatments. Their study also lends support to the effectiveness, acceptability, and practicality of iCBT for treating anxiety disorders. A number of randomized controlled trials (RCTs) have demonstrated the effectiveness of guided iCBT in reducing general and social anxieties, avoidance, depression, and dysfunctional thinking, as well as improving the quality of life and functioning of people with SAD [15-19]. Guided iCBT programs for SAD have shown promising diagnostic response rates [20] with complete and partial recovery rates of 34.2% and 36.8%, respectively, upon completion of the treatment [19]. The positive treatment effects are maintained at the 6-month [19], 1-year [15], 2-year [21], and 4-year [22] follow-ups. Therapist contact is reportedly a significant predictor of intervention outcomes in guided iCBT programs for SAD [23]. Therapist support is usually provided via telephone, email, videoconferences, SMS text messages, and web-based discussion forums [17,24].

The intervention skills in the various iCBT programs for SAD generally include psychoeducation, cognitive restructuring, behavioral experiments, exposure and reality testing, modifying attention bias, social skills training, developing healthy lifestyles, problem-solving, and preventing relapses [15,20,21]. The presentation formats of the iCBT program involve text, images, audio, video, text entry fields, animation, comic slides, e-books, etc [24]. Interventions include monitoring moods, performing exposure exercises and homework assignments, writing a web-based diary, answering essay questions, participating in user forums, and receiving emails or text message reminders, and awards [17,18].

### VRET for SAD

One of the central components of CBT for SAD is exposure therapy in which clients are exposed to social stimuli that cause anxiety while eliminating safety behaviors so that they learn and understand that the anticipated negative consequences are ill-founded [3]. Exposure therapy can activate and modify anxious responses by having individuals confront the fear stimuli and via habituation and extinction learning, respectively, in which the fear stimuli then cease to provoke anxious responses or render them less threatening. Given that in vivo exposure therapy in real life is not frequently offered, VRET has become an important alternative for reproducing social situations [3]. Computer graphics, body tracking devices, visual displays, and other sensory input devices are integrated to immerse clients in a computer-generated virtual environment [25]. As virtual reality (VR) can elicit moderate levels of sense of presence and anxiety during virtual social interactions [26], VRET has become a promising application for treating SAD.

Meta-analyses have consistently found a significantly large effect size for VRET compared to a waitlist or psychological placebo conditions for SAD treatment, and no significant difference in effect size between VRET and in vivo or imaginal exposure therapy [27,28], thus indicating that VRET is effective for SAD treatment with effects comparable to those of traditional exposure therapy. Specifically, VRET is effective in reducing social anxiety symptoms, such as fear and avoidance, fear of negative evaluation, self-reported public speaking anxiety, catastrophic belief expectancy, probability and cost biases, distress, perceived stress, and depressive symptoms, and increasing the length of speech time, perceived performance quality, and confidence [2,16,29,30]. The positive effects are maintained at the 3-month, 6-month, 12-month, 5.5-year, and 6-year follow-ups [29,31,32]. More than half of treated individuals no longer meet the diagnostic criteria for SAD (54%) and self-reported to be “very much” or “much” improved (68%) 6 years after treatment [31]. Thus, VRET is considered an efficacious alternative to in vivo exposure therapy [27].

Both psychological and physiological indicators are measured in VRET studies. The commonly used psychological indicators include self-reported anxiety and fear, distress, and self-confidence [33,34]. As anxiety often emerges in the form of physical symptoms, VRET studies have measured physiological responses, such as blood oxygen level [35] and heart rate [36].

### This Study

Technology-assisted CBT programs have great potential to extend mental health services to people with social anxiety who are unwilling or unable to seek face-to-face therapy [23]. However, these programs are underdeveloped in Chinese societies, such as Hong Kong. This study has, therefore, developed an iCBT program with VRET, called “Ease Anxiety in Social Event Online” (Ease Online), for Hong Kong adults with SAD in an RCT.

## Methods

### Participants

To be included in the study, participants should be Hong Kong residents who (1) are fluent in Cantonese, (2) are aged between the 18 and 70 years, (3) obtained a score of 24 or higher on the Chinese version of the Social Phobia Inventory (SPIN) [37], (4) have a social anxiety disorder as assessed by the Structured Clinical Interview for disorders listed in the Diagnostic and Statistical Manual of Mental Disorders, 4th Edition [38], (5) have not received any psychological treatment at the time of registration for participation in this study, (6) have access to a computer or smartphone with an internet connection, and (7) have a valid email address. We will exclude individuals who have (1) severe depression, with a score above 30 on the Beck Depression Inventory-II (BDI-II) [39]; (2) suicidal risk in the past 3 months (score of item 9 on the BDI-II is “2” or “3” and assessed to have suicidal risk in the intake interview); and (3) a severe psychiatric condition (eg, bipolar disorder, schizophrenia, or personality disorder) diagnosed by a psychiatrist or clinical psychologist.

### Sample Size

The sample size was calculated by using a computer program called G*Power (version 3.1.5; Universität Düsseldorf). The statistical method used was a multivariate ANOVA with repeated measures (within-between interactions). The effect size was assumed to be 0.40 (large) [40]. The number of groups was 3 (2 experimental groups and 1 control group) and 7 measures applied (please see the *Outcome Measures* section). The α value was set at .01. The calculations resulted in a minimum sample size of 139. This study aims at recruiting 330 eligible participants, with 110 in each experimental group and the waitlist control (WLC) group, respectively.

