### Data Analysis

Intent-to-treat analysis, which is the least biased way to estimate an intervention’s effects [57], was used for data analysis. Missing data will be managed using multiple imputation [58]. Multivariate ANOVA with repeated measures will be performed to test the intervention’s effectiveness on continuous variables over time. Time (pretest, posttest, and 3- and 6-month follow-ups), condition (web-based iCBT, app-based iCBT, and WLC), and the interaction of time-by-condition will be specified as the categorical fixed factors. Medication and demographic factors (eg, gender, age, and marital status) will be specified as fixed covariates to control the potential confounding effects. Cohen *d* will be calculated as the index of the effect size both within and between groups.

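### The stated minimum of 139 appears to count the seven questionnaires as repeated measurements; the planned test has four occasions, for which the same inputs give 114

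*Protocol article*

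**What the plan says.** The Sample Size section of the protocol article names G*Power and the test: "The statistical method used was a multivariate ANOVA with repeated measures (within-between interactions"). The assumed effect is given as "The effect size was assumed to be 0.40 (large"), and alpha is .01. The design counts read: "The number of groups was 3 (2 experimental groups and 1 control group) and 7 measures applied", with a pointer to the Outcome Measures section. The result is "The calculations resulted in a minimum sample size of 139". The next sentence sets the target: "This study aims at recruiting 330 eligible participants, with 110 in each experimental group" and the same number in the waitlist group. No power is stated, and nothing links 330 to 139.

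The Outcome Measures section describes seven questionnaires: SPIN, C-BAI, BDI-II, GHQ-12, the Automatic Thoughts Questionnaire, the WHO quality of life scale and the Internalized Stigma scale.

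The Data Analysis section defines the within-person factor as "Time (pretest, posttest, and 3- and 6-month follow-ups"), crossed with three conditions. The Research Design section confirms that all three groups share these four occasions. The waitlist group has one extra test, which makes five for that group alone.

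**The concern.** For a within-between interaction in a repeated-measures MANOVA, the second design count is the number of times the same variable is measured on each person. It fixes both degrees of freedom of the test. The number of different instruments does not enter that procedure. The article gives 7, ties it to the list of instruments, and describes no design with seven occasions.

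If the instrument count was entered where the occasion count belongs, 139 describes a design that this trial does not have. It is the only calculated figure supporting the trial's size. A reader therefore cannot tell from the article what the planned test can detect, or at what power.

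**Working it through.** **Inputs.** From the Sample Size section: k = 3 groups, effect 0.40 (taken as f(V), the effect measure of this G*Power procedure), alpha = .01, 7 measures. From Data Analysis: 4 occasions. Power is not stated, so .80, .85, .90, .95 and .99 were tried.

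**Formula.** Pillai trace with the O'Brien-Shieh noncentrality, for m measurements:

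- s = min(k − 1, m − 1)
- df1 = (k − 1)(m − 1)
- df2 = s(N − k − (m − 1) + s)
- λ = N · s · f(V)²
- power = P(F′(df1, df2, λ) > F critical at .01)

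**Step 1: reproduce 139.** With m = 7: s = 2, df1 = 2 × 6 = 12. At N = 139, df2 = 2 × (139 − 3 − 6 + 2) = 264 and λ = 139 × 2 × 0.16 = 44.48. Critical F = 2.253 and power = 0.9904. At N = 138 power is 0.9898, just under .99. So N = 139 is exactly the minimum for power .99.

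**Step 2: is the match unique?** With this formula, over m = 2 to 8, alpha .01 and .05, and the five powers above, no other combination gives 139.

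**Step 3: change only the number of measurements to 4.** s = 2, df1 = 2 × 3 = 6. At N = 114, df2 = 2 × (114 − 3 − 3 + 2) = 220 and λ = 114 × 2 × 0.16 = 36.48. Critical F = 2.885 and power = 0.9902; at N = 113 it is 0.9895. The minimum is 114.

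| Power | 7 measurements | 4 occasions |
|---|---|---|
| .80 | 81 | 64 |
| .90 | 97 | 77 |
| .95 | 110 | 89 |
| .99 | 139 | 114 |

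At power .99 the stated figure is 139/114 = 1.22 times that of the planned test.

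**Step 4: other readings of the 7.** Counting the extra waitlist test as a fifth occasion gives 123 at power .99, not 139. One joint test of seven outcomes over three time contrasts needs 134, 156, 175 and 213 at power .80, .90, .95 and .99. At N = 139 that test has power of about 0.83, so it does not yield 139 at any of these powers either.

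**Step 5: a different noncentrality.** With λ = df2 · f(V)², 7 measurements at power .99 give 145 and 4 give 118. This does not reproduce 139, but the gap between 7 and 4 is much the same.

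**Step 6: consequence for the trial.** With 4 occasions and f(V) = 0.40, power is 0.998 at N = 139 and above 0.9999 at N = 330. Solving the same formula for f(V) at 80% power and alpha .01 gives 0.17 at N = 330. If half the data were lost (an assumption, N = 165), it gives 0.24.

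**The case against.** The best defence is that the error changes nothing in the trial. For the planned four-occasion test it raises the minimum rather than lowering it, and the target is 330/139 = 2.4 times the stated minimum. By February 2023, 329 participants had joined. The sample could lose (330 − 139)/330 = 58% and still hold 139, or (330 − 114)/330 = 65% and still hold 114. All of this stands, and it limits the severity.

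It is also fair that the power of .99 is inferred, and that leaving it out may be condensation in a journal article. The exact match makes the mechanism likely but does not prove it. The conflict between seven measures and four occasions is on the page whatever the power.

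Three stronger readings are tempting, and the documents do not support them.

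- A reader might infer that the trial is underpowered. At f(V) = 0.40 it is not.
- Because the waitlist group is treated right after posttest, a reader might rerun the calculation for pretest and posttest only, find a larger number, and call 139 too small. That treats f(V) = 0.40 as the same treatment effect whatever the number of occasions, which it is not. The two-occasion test is also not the planned model.
- A reader might fault 330 itself, or the absence of an attrition term, given the high amount of missing data reported under Limitations. Recruiting above a stated minimum is not an error, the margin is wide, and that missingness was observed during the trial rather than available as a planning input.

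**Conclusion.** The point holds in a limited form. The minimum of 139 appears to result from entering the seven questionnaires as repeated measurements. The planned time-by-condition test has four occasions, and the same inputs then give 114. The stated figure is therefore 25 participants, or 22%, above that of the planned test.

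This rests on reading the effect of 0.40 as f(V), on the O'Brien-Shieh noncentrality, and on an inferred power of .99. The mismatch between the stated input and the planned model depends on none of these.

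Severity is minor to moderate. The error is conservative, 330 exceeds both figures, and neither recruitment nor the analysis is affected. The harm is that the published justification of the sample size does not belong to the planned test.

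**What to change.** Rewrite the Sample Size paragraph:

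- Replace 139 with the figure for 3 groups and 4 measurements, and state the power used: 114 at power .99, or 64, 77 or 89 at .80, .90 or .95, with f(V) = 0.40 and alpha .01.
- Keep 330 and say what it delivers for the planned test. At 80% power and alpha .01 the detectable f(V) is about 0.17 with complete data. Give the corresponding value after an explicit missing-data allowance, for example about 0.24 if half the data were lost.
- Optionally, add the detectable SPIN difference against waitlist at posttest, with its assumptions. This supplements the planned model and does not replace it.

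The cost is one paragraph and a rerun of the same software. Recruitment and the analysis model stay as they are.

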### Participant Recruitment and Screening

Participants were recruited from the general population on an ongoing basis through various means, such as advertisements on social media (Facebook and Instagram) and Google, press conferences, posters, and referrals from local nongovernmental organizations. Interested participants were asked to complete a screening questionnaire that includes the Chinese version of the Beck Anxiety Inventory (C-BAI), BDI-II, and Chinese version of the SPIN on the program website [41]. Initially qualified participants were invited for a 1.5-hour intake interview in person or via Zoom with a psychological counselor or an experienced social worker for further assessment of suitability for participation (including assessment of suicidal risk and social anxiety disorder based on the diagnostic criteria of the Structured Clinical Interview for disorders listed in the Diagnostic and Statistical Manual of Mental Disorders, 4th Edition [38]). Marginal cases were discussed in a case meeting (which involved author [name], an intake worker, and a program therapist) for participation eligibility. A project assistant contacted the eligible participants to reconfirm their desire to participate before randomization took place. High-risk individuals with severe depression or suicidal risk (or both) identified at the screening stage were referred to the local mental health service sectors for further diagnosis and treatment with their consent.

### Research Design

Although deterioration in a control condition can take place [42], Steinert et al [43] conducted a meta-analysis and found only small changes in the WLC groups during short-term wait periods for clients with SAD in RCTs. Thus, this study adopts a WLC group design to conduct a 3-arm RCT as shown in Table 1.

There were 2 experimental groups that joined either the web-based or app-based iCBT program (Ease Online). The WLC group received the app-based treatment immediately after the 2 experimental groups completed the program. All 3 groups completed the same web-based questionnaire at pretest, posttest, and 3- and 6-month follow-ups. The WLC group completed the questionnaire one more time at posttest after the 2 experimental groups completed the program. To increase the submission rate of questionnaire, participants were given 2 more weeks to submit an email questionnaire after the submission deadline in the program system. The RCT was conducted in cohorts for implementation feasibility. Specifically, in each cohort, around 30 qualified participants were randomized into one of the 3 groups through computer-generated random numbers, with approximately 10 in each group. The program evaluators were blinded to the allocation of the participants. The participant recruitment flowchart is shown in Figure 1.

**Table 1 table1:** Participant group design.

Groups	Research design						
Web-based	O^a^	X^b^	O		O	O	N/A^c^
App-based	O	X	O		O	O	N/A
Waitlist control	O		O	X	O	O	O

^a^O: test.

^b^X: intervention.

^c^N/A: not applicable.

